### Clinical implications

Given the constant and equal number of recurrences in both groups, if patients submitted to laparoscopic repair have the same results in physical testing in comparison with open repair, then the trial would indicate (*acceptance of the null hypothesis*) that an anatomic repair of incisional hernia through rectal muscles medialization does not offer any advantage to the patient. The reasons for this deduction could be twofold: first, the anatomic repair is not effective on previously scarred tissue, and, second, the dimensions of the defect included in this trial are too small to determine a perturbation of the abdominal motility. The clinical implications for these results would be that the laparoscopic bridging hernia repair in patients over 60 years of age should be considered a valid alternative to open repair, for both its efficiency and functional, or even superior, results given the advantages already demonstrated in previous trials (fewer wound complications, shorter postoperative hospital stay). It would remain an open question whether the restoration of the anatomic abdominal structure would be useful in younger patients. If the results reveal a better test performance in the anatomic reconstruction group (*rejection of a null hypothesis*), the choice of this type of intervention as the gold standard technique would be supported by clear evidence of an advantage offered in terms of the functional restoration of the abdominal wall.

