Surprisingly and in opposition to previous studies included in the Cochrane review, a recently published randomized trial [16] indicated that postoperative pain and recovery at 3 weeks is not affected by the type of adopted hernia repair, but the laparoscopic approach results in better physical function than the open repair based on SF36 subscale values. This observation is only partly the consequence of the reduced number of surgical site infections following laparoscopy. Moreover, these findings could support the hypothesis that procedures aimed at restoring the anatomy that involve extensive and potentially damaging dissection in an already scarred myoaponeurotic region could be less effective for the patient. In other words, in certain circumstances, anatomic reconstruction could be an excessive burden for an already compromised abdominal wall. Nevertheless, a self-reported questionnaire cannot be accepted as the sole explanation of this phenomenon, which should be objectively investigated and measured.

To obtain an answer to the debate, an emerging type of analysis is being more frequently used: the functional evaluation of the motility and muscular strength of the abdominal wall. The modalities to evaluate the trunk flexor muscles and the strength of the abdominal wall are isokinetic dynamometer measurement and physical testing.

The isokinetic dynamometer (Biodex Model 2000, Multijoint System 3, Biodex Corp., Shirley, NY, USA) is a safe way to load a dynamically contracting muscle to maximum capability throughout its entire range in a continuous motion and to evaluate the trunk flexor strength during isokinetic movement at a constant angular velocity. An inexpensive alternative to using a machine for evaluation is the use of physical tests. The most commonly used tests are the double leg-lowering test (DLL) and the trunk-raising test (TR). Both of them explore the strength of the rectal muscle, asking the patient to perform some curl-type exercises. After categorization of DLL and TR, it is possible to create an abdominal wall strength score (AWS) with a minimum score of 0 and a maximum of 10 points.

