### Aim of the study

The aim of this study is to define the role of anatomical reconstruction and simple defect bridging in the mesh repair of incisional and primary ventral hernias. We wanted to analyze in depth whether defect bridging is comparable to anatomical reconstruction with mesh in terms of the strength of the abdominal wall as expressed by the differences among groups 1 year postoperatively in the grades of leg extension over the trunk during a DLL test.

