## Design

LABOR is a randomized, controlled, non-inferiority trial. Patients will be randomly allocated to receive a mesh repair of their incisional hernia with either laparoscopic bridging or open anatomical reconstruction. The trial has been registered on Current Controlled Trials as ISRCTN93729016.

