### Interventions: surgery

The patient will be divided into two groups according to the randomized procedure:

Group R (reconstruction)

The planned number of patients will be submitted to a Rives-Stoppa procedure for the repair of the defect [22].

Group B (bridging)

In this group, after randomization patients will be operated on using a standard laparoscopic technique [23].

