### Mesh

To minimize the effect due to different materials and density, every center will be encouraged to use the same type of mesh. A composite, lightweight, polypropylene mesh suitable for both retromuscular and intraperitoneal repair should be adopted.

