### Fixation methods

The mesh will be sutured in Group R with standard, non-resorbable passing sutures. In Group B, absorbable tacks placed with the double crown technique and reinforced with fascial sutures will be used.

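### Equal results could not show that midline closure itself gives no advantage, because the arms also differ in access, fixation and, by inference, mesh plane

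*Protocol article*

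**What the plan says.** The Design section states "LABOR is a randomized, controlled, non-inferiority trial" and names the arms as laparoscopic bridging and open anatomical reconstruction. For Group R, Interventions: surgery says "The planned number of patients will be submitted to a Rives-Stoppa procedure for the repair of the defect". For Group B it says "In this group, after randomization patients will be operated on using a standard laparoscopic technique".

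Fixation methods gives Group R non-resorbable sutures. For the other arm it says "In Group B, absorbable tacks placed with the double crown technique and reinforced with fascial sutures will be used". The Mesh section asks all centres for one type of mesh, but one "suitable for both retromuscular and intraperitoneal repair should be adopted".

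The Aim of the study is to "define the role of anatomical reconstruction and simple defect bridging in the mesh repair of incisional and primary ventral hernias", and access route is not mentioned there. The Abstract hypothesises that, for defects of this size, anatomical reconstruction adds almost nothing. The Background sets up the debate as whether bringing the rectus muscles to the midline improves abdominal wall function.

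Clinical implications then says that, given equal recurrence, the same physical-test results in both arms would indicate "that an anatomic repair of incisional hernia through rectal muscles medialization does not offer any advantage to the patient". It offers two reasons for such a result: the repair does not work on scarred tissue, or the defects are too small to disturb motility.

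**The concern.** The question is posed about one component, restoration of the midline, but the arms differ in several components at once. No arm has an open bridge or a laparoscopic closure, so closure and access are completely aliased.

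This matters because the protocol itself names a force in the opposite direction. The Background says that "procedures aimed at restoring the anatomy that involve extensive and potentially damaging dissection in an already scarred myoaponeurotic region could be less effective", and the Discussion favours bridging for small defects partly because it needs less dissection and is less invasive. If closure helps and dissection harms, the two can cancel. A reader would then be told that medialization gives nothing, when the trial had shown only that the two operations come out even. That error could occur in a perfectly conducted trial.

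**Working it through.** **1. What differs between the arms**

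| Component | Group R | Group B | Basis |
|---|---|---|---|
| Midline | reconstructed | bridged | Design; Interventions: surgery |
| Access | open | laparoscopic | Design |
| Fixation | non-resorbable sutures | absorbable tacks plus fascial sutures | Fixation methods |
| Mesh plane | retromuscular | intraperitoneal | inferred |

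The mesh plane is not stated arm by arm. It follows from three places: the Background classes Rives-Stoppa as a retrorectus repair, Interventions: surgery assigns it to Group R, and the Mesh section requires a mesh fit for both planes. The material is harmonised; the plane is not. Surgical period adds differences in drains and wound infiltration, on which this point does not rely.

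**2. What the planned sample size addresses**

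Inputs from the sample size section: margin 5 degrees, SD 8.5 degrees, power 90%, alpha 5%. With a true difference of zero and a one-sided 5% test:

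n per arm = 2 × (1.645 + 1.282)² × 8.5² / 5² = 2 × 8.567 × 2.89 = 49.5, rounded up to 50.

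This reproduces the stated 50 per arm. The document does not state whether alpha is one-sided or two-sided, which is a separate matter. The calculation concerns one quantity only, the difference in mean DLL between the two arms.

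**3. What that difference contains**

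On an additive model, write m for the effect of midline closure and o for the combined effect of everything else that comes with the open arm (access, dissection, plane, fixation). Then

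D (open minus laparoscopic) = m + o.

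Each component is present in all of one arm and none of the other, so all components share the same indicator. Two arm means give one contrast. The sum m + o can be estimated; m alone cannot, at any sample size.

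**4. What D = 0 implies**

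D = 0 gives m = −o. It gives m = 0 only if o = 0, which nothing in the document establishes and the Background's remark on dissection disputes.

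For illustration only, with assumed values:

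- m = 0, o = 0: D = 0
- m = +5, o = −5: D = 5 − 5 = 0

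The two cases give the same expected difference. If o lay anywhere from −5 to 0, the closure effect compatible with D = 0 would run from 5 to 0. The 5 degrees is the margin borrowed as a scale. The document gives no effect size for either component.

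**5. Does the text allow for this?**

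Neither of the two listed reasons for a null result is an offset between closure and the rest of the operation. Yet the Blinding section treats approach (laparoscopic or open) and type of repair (reconstruction or bridging) as separate attributes, and the Mesh section standardises material because material could affect results. The document therefore recognises the components as distinct, but draws its null conclusion about only one of them.

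**The case against.** The best reply is that the sentence can be read at procedure level. It is conditional on laparoscopic and open repair performing alike, and its subject is an anatomic repair, with medialization describing how that repair works. If closure helps and dissection cancels the gain, the repair as performed does give no net advantage in DLL, and the sentence is true. Much of the rest is also at procedure level: the title and Design name both packages, the Abstract specifies open access for the re-approximation arm and treats a null result as leaving a choice between interventions on cost and experience, and Clinical implications goes on to call laparoscopic bridging a valid alternative to open repair. Dissection is part of what reconstruction costs the patient, and differences in access and fixation are inherent in comparing two established operations.

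Most of this stands, and it limits the point to interpretation. It does not remove it. The Abstract, Background and Aim ask about reconstruction or medialization as such, so readers will take the sentence as the answer to that question.

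A reader might also infer that the plan would credit medialization alone if open repair does better. The text does not say so: it would then support that type of intervention as the gold standard, which is close to a procedure-level claim. Nor does it say anything about closing the midline by other routes, so a warning that such closure would be discouraged would be speculation.

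**Conclusion.** The point holds as one of attribution. The trial can estimate the net difference between laparoscopic bridging and open Rives-Stoppa reconstruction. It cannot support a conclusion that medialization itself gives no advantage, because equal results are equally compatible with a benefit offset by other features of the open operation.

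The size of any offset is unknown. The 5-degree figures above are assumptions and should not be quoted as an estimate of error. The verdict rests on the access and fixation differences, which are explicit; the mesh-plane difference is inferred and not essential.

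A reader might infer that the randomised comparison is confounded or the trial invalid. The document does not support that: allocation is randomised, the comparison of the two procedures as delivered is valid, and the conclusions drawn at that level are within its reach. This should be fixed, but it is not a flaw in the design, endpoint, sample size or analysis.

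**What to change.** In Clinical implications, and for consistency in the Abstract's hypothesis and the Aim of the study:

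- state the question and the conclusions as laparoscopic bridging versus open Rives-Stoppa reconstruction, as delivered;
- remove the inference that medialization itself offers no advantage;
- add offsetting effects of access, dissection, mesh plane and fixation to the listed explanations of a null result.

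Arms, sample size, endpoint and data collection do not change. The cost is a few sentences and a narrower claim about mechanism.

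Relating DLL to the interrectal distance on the 12-month CT would not be a remedy. That distance is likely to track treatment arm closely, so the analysis would carry the same aliasing.

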### Sample size calculation, randomization and statistical analysis

On the basis of a previous published work, the minimum DLL to define the non-inferiority of laparoscopic bridging vs. anatomic open reconstruction will be set to 5 degrees with a standard deviation of 8.5 degrees. With this hypothesis and for a power of 90% and an alpha of 5%, we will need 50 patients in each arm (total 100). If we consider a possible dropout rate of 10%, a total of 110 patients would be sufficient. As a consequence, approximately 20 patients for each center will be required.

A centralized block randomization stratified for center will be performed by a statistician not involved in patient management. Blocks will have a variable dimension (random) between 4 and 12 units. A total of five blocks will be obtained for each center in the event that the investigator continues enrollment beyond the initially planned sample size. The local investigators, after obtaining written informed consent of patients, will receive the randomization arm from the statistical center for each patient, then the patient will be allocated to the treatment group as indicated.

Data analysis will be performed by a statistician not involved in data collection at the main investigation center (University of Genoa). The means and standard deviations or medians with ranges, if asymmetry of data is detected, will be reported for all continuous demographic and clinical characteristics recorded, whereas counts and percentages will be recorded for categorical characteristics (e.g., gender, functional status and smoking habits).

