Moreover, with the rapidly increasing use of laparoscopy, the numbers and size of incisional hernias have been reduced. Consequently, it can be postulated that two types of abdominal wall defects are currently more frequently encountered: small (<10 cm in their major diameter) primitive and incisional hernias and giant abdominal hernias. Given the aforementioned hypotheses, a patient with a small defect would receive an advantage from a simple bridging of the defect with mesh. This effect would be better indicated in comparison with an anatomical reconstruction for the inferior burden in terms of dissection, the reduced operative time and the possibility of using a less invasive approach. In contrast, a giant abdominal defect has a larger impact on the anatomy, abdominal wall compliance and the personal image of the patient. Moreover, the predicted muscular damage to the abdominal wall could be relevant. Future research needs to be conducted to determine whether, in these cases, a simple bridging would be equivalent or superior to an anatomical reconstruction and to evaluate the effects on abdominal wall function recovery.

We decided to adopt the outcome of DLL because it represents a more straightforward method to define the ability of a procedure to restore abdominal wall function. In fact, we have considered that a dynamometer is the ideal way to measure a difference because it offers a quantitative calculation of a variable that can be compared among different groups. However, as occurs for other medical variables, a significant difference could be clinically irrelevant.

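### The conclusion in favour of open reconstruction rests on rejecting no difference, without reference to the 5-degree non-inferiority margin or the size of the difference

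*Protocol article*

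**What the plan says.** The Design section states: "LABOR is a randomized, controlled, non-inferiority trial". Under Sample size calculation, randomization and statistical analysis, the margin is fixed: "the minimum DLL to define the non-inferiority of laparoscopic bridging vs. anatomic open reconstruction will be set to 5 degrees". The SD assumed there is 8.5, and the resulting size is "50 patients in each arm".

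The analysis paragraphs of that section plan a repeated-measures ANOVA with significance at p below 0.05. They do not mention the margin.

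The Clinical implications section reads the trial through a null hypothesis. Accepting it means that anatomic repair offers no advantage. The other branch begins "If the results reveal a better test performance in the anatomic reconstruction group", which the text equates with rejection of the null, and concludes that "the choice of this type of intervention as the gold standard technique would be supported by clear evidence of an advantage". No minimum difference is attached. The abstract's Discussion also frames the null as no difference between treatments.

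Shortly before, the Discussion remarks that "a significant difference could be clinically irrelevant".

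**The concern.** A non-inferiority trial has two reference points on the outcome scale: zero and the margin. Here the margin sizes the trial and then drops out of the conclusions. The open-repair branch depends only on whether zero is excluded.

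The null in that branch cannot be the non-inferiority null. Rejecting the non-inferiority null would favour bridging, whereas the text says that rejection favours open repair.

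At stake is the trial's pre-stated message for patients over 60. A result that excludes zero but leaves it unknown whether the loss is above or below 5 degrees would be reported as settling which operation is the standard.

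**Working it through.** **Inputs** (sample size section): margin 5 degrees, SD 8.5, power 90%, alpha 5% with sidedness not stated, 50 per arm. A higher DLL score is better, so the difference is taken as open minus bridging, and a positive value is a loss with bridging.

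**The plan's own sample size.** n per arm = 2 × [SD × (z_alpha + z_power) / margin]².
- One-sided 5%: 2 × [8.5 × (1.645 + 1.282) / 5]² = 49.5, so 50. This matches the plan.
- One-sided 2.5%: 2 × [8.5 × (1.960 + 1.282) / 5]² = 60.7, so 61.

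The stated size therefore implies a one-sided 5% test.

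**Smallest significant difference.**
- SE = 8.5 × √(2/50) = 1.70 degrees.
- Two-sided 5%: 1.96 × 1.70 = 3.33 degrees (3.37 with t on 98 df). With 55 per arm it is 3.18.
- One-sided 5%, 50 per arm: 1.645 × 1.70 = 2.80.

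**What such results say about the margin** (50 per arm; t-based intervals for 3.4 and 4.0).
- Observed 3.33: 95% CI about 0 to 6.7.
- Observed 3.4: p = 0.048, 95% CI 0.03 to 6.77.
- Observed 4.0: p = 0.021, 95% CI 0.63 to 7.37.

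All three exclude or just touch zero, and all include 5.

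**Can one dataset give both verdicts?** Non-inferiority needs the upper limit below 5.
- Two-sided 95% interval: observed loss below 5 − 3.33 = 1.67.
- One-sided 5%: observed loss below 5 − 2.80 = 2.20.
- Significance for open repair needs more than 3.33.

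The ranges do not overlap at the planned size and SD. With the 95% interval they overlap only if 2 × 1.96 × SE < 5, so SE < 1.276 and SD < 1.276 / 0.2 = 6.4. If non-inferiority is judged at one-sided 5%, (1.96 + 1.645) × 0.2 × SD < 5 gives SD < 6.9.

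Baseline adjustment could bring the SD that low. With an assumed correlation of 0.7 and 8.5 as the unadjusted SD, the residual SD is 8.5 × √(1 − 0.49) = 6.07 and 1.96 × SE is 2.38. An observed difference between 2.38 and 5 − 2.38 = 2.62 would then be both significant and non-inferior.

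**How often the open-repair branch is reached.** P(observed > 3.33) for a true advantage of 2, 3 or 4 degrees is 22%, 42% and 65%. These figures are power to detect a real difference smaller than the margin.

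**The case against.** **The margin is judged against a confidence limit, not a point estimate.** A reader might infer that an observed 3.3 degrees is a result the plan calls acceptable, so that the two branches contradict each other on the same data. The documents do not support this. At 3.3 degrees the upper limit is about 6.7, non-inferiority fails, and at the planned size and SD no dataset yields both verdicts. This objection stands in full.

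**Rejecting no difference is correct when open repair is truly better.** A reader might take the 22%, 42% and 65% as rates of wrong conclusions. They are not: with a true advantage of 2 to 4 degrees, open repair is better on DLL. Only the relevance of the difference is open. This stands too.

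**A superiority claim is conventionally tested against zero.** The margin may express a loss tolerated in exchange for the fewer wound complications and shorter stay that the article cites. That is fair, and it is why a claim that open repair is better on DLL need not wait for the whole interval to exceed 5. Such a demand would need an observed difference of about 5 + 3.33 = 8.3 degrees. A true advantage of 5, 7 or 8 degrees would pass only about 2.5%, 22% and 42% of the time. The convention does not, however, carry a finding of some difference up to gold-standard status.

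**The caveat on clinical relevance has a context.** It follows a remark about the dynamometer and helps explain the choice of DLL. It is worded for medical variables generally, but it is not a decision rule that the plan breaks.

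**The passage is discussion prose and names no p-value.** The link to p below 0.05 is an inference from the analysis paragraphs, the only place that gives a threshold. The text also limits the advantage to functional restoration of the abdominal wall. Both points soften the wording, but neither brings in the margin or a size.

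**Conclusion.** The concern holds as an interpretation rule that ignores the plan's own margin. The trial is designed around 5 degrees, yet its conclusion for open repair turns only on excluding zero, which takes an observed difference of about 3.3 degrees. At that point the interval runs from about 0 to 6.7. Open repair is shown to be better on DLL, non-inferiority of bridging is not shown, and the relevance of the difference is unsettled.

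The figure assumes a simple two-group comparison with 50 per arm, SD 8.5 for the quantity analysed, and a two-sided 5% test. The article does not say whether 8.5 refers to DLL values or to changes, and a rank-based analysis would have no fixed threshold in degrees. Within the simple comparison the finding is robust. The threshold stays below 5 until the SD reaches 5 / (1.96 × 0.2) = 12.8, and baseline adjustment would lower it.

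This is a fault worth correcting before results are known. It does not affect the conduct of the trial.

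**What to change.** Rewrite the Clinical implications section so that each conclusion follows from the confidence interval for the 12-month DLL difference (open minus bridging) relative to 0 and 5 degrees:

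- Upper limit below 5: bridging non-inferior. If the interval also excludes 0, say so and in which direction.
- Interval above 0 but including 5: open repair better on DLL, non-inferiority not shown, clinical relevance unsettled.
- Interval including both 0 and 5: inconclusive.
- Whole interval above 5: bridging inferior by more than the margin.

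Do not attach gold-standard or clear-evidence wording to p below 0.05 alone. Make the same change where the abstract speaks of accepting the null.

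State the confidence level as well. With 50 per arm and no true difference, power for non-inferiority is 90% at one-sided 5%, but about 84% if the two-sided 95% interval is used.

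The cost is wording. There is no change to conduct. The one real loss is that a significant result whose interval includes 5 supports a more cautious statement for open repair than the present text allows.
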